#### 2.1.11. Recruitment

The sample of choice will be neonates with the breech presentation during late pregnancy, after screening for inclusion/exclusion criteria and obtaining informed consent.

### 2.2. Methods: Assignment of Interventions

#### 2.2.1. Allocation

Once the sulcus angle measurements have been studied by an ultrasound, a random block sampling will be performed with the “Study Randomizer” software (https://www.studyrandomizer.com/ accessed on 14 December 2022). The pediatric orthopedic surgeon will index the patient history number that identifies each subject in this software. The software then generates a hidden sequence, which assigns a group to each subject. The analyst will also be blinded by the hidden assignment sequence used by the software.

#### 2.2.2. Blinding

Patients’ caregivers cannot be blinded to the treatment with the Pavlik harness. However, the patient will attend the ultrasound tests and the pediatric orthopedic surgery check-ups without the harness. The clinical analyst will be blinded by the software that keeps the assignment sequence associated with each subject hidden.

### 2.3. Methods: Data Collection, Management, and Analysis

#### 2.3.1. Data Collection Methods

Ultrasound examination will be performed with the patient in a supine position and the knee placed at 45–90° of flexion. The positioning of the transducer must be in a transversal plane perpendicular to the axis of the femoral diaphysis. This way, the femoral condyles, the trochlea, and the ossification centre are visible.

Likewise, the following variables will be documented:Age;Sex;Birth weight;Birth presentation (footling, frank or complete breech);Presentation at the last ultrasound performed during pregnancy;Coxofemoral joint status according to clinical (Graf classification [39]: I = normal, II = unstable, III and IV = off-centre) and sonographic parameters (α angle).

Based on the review by the pediatric orthopedic surgeon, the following variables will be controlled:Verification of the suitable position of the harness during the check-ups performed every four weeks until two months;Treatment difficulties and adverse reactions: blistering, inadaptation, crying, femoral nerve palsy, avascular necrosis of the femoral head;The discrepancy of inferior limb length;Skin folds asymmetry;Knee articular balancing: complete and symmetrical, uncomplete of one knee, uncomplete of both knees;Articular click;Patellar displacement: tolerated, apprehension in the form of crying or discomfort.

#### 2.3.2. Data Management

All relevant data of the study subjects will be transcribed with a blue pen to the Data Recollection Notebook (DRN). The DRN must be filled entirely and in legible handwriting to later perform the statistical analyses. Once the study is finished, all data collected will be evaluated for the final report writing.

All the study documentation will remain stored in the researcher’s archive of the participant centre, in the custody of the principal investigator (PI) until the finalization of the study. Once finished, the documents will be indexed and stored in the centre’s general archive, according to the recommendations of good clinical practice.

The PI will take care of the conservation of the identification codes for at least fifteen years after the study is finished or interrupted.

The promoter or the data owner will preserve all the documentation relative to the study for the time required by the law.

In any case, the confidentiality of the data and documents in the file will be ensured.

Data from all DRNs will be entered into a database created for this purpose and provided with security margins and internal consistency rules. This database shall be equipped with a double-entry system and filters to prevent and detect any inconsistencies or errors in the database. The information will be validated by internal consistency checks, looking for missing values. Data will be checked and corrected until the database is fully validated.

Once the database is cleaned, the variables will recode by generating new variables (regroupings, summations, etc.).

#### 2.3.3. Statistical Methods

The primary efficacy endpoint is the comparison of the treatment with the Pavlik harness for two months, measured by analyzing the initial ultrasound sulcus angle data and those obtained after the treatment period.

The Shapiro–Wilk test will be performed to assess the normality of data.

To determine if the Pavlik harness is more effective in reducing knee SA compared to no treatment, the results of the intervention group will be compared to the control group with the Student’s t-test for independent data. The intervention will be effective if it achieves statistical differences (with a 95% confidence) in the knee SA between the treatment and control groups before and after treatment.

To assess if the Pavlik harness is effective in reducing the knee SA within the treatment group, the Student’s t-test for dependent data will be applied to compare the values of the ultrasound sulcus angle at baseline and two months within each group (treatment and control).

A regression analysis will be performed to determine the relationship between the use of the Pavlik harness and knee SA while accounting for other factors that may affect the knee SA.

The difference in the proportion of participants between the two treatment arms who are classed as a treatment success at two months will be calculated with Fisher’s exact test of independence.

Missing data shall be treated using the multiple imputation procedure to identify patterns in the dataset’s missing data and replace missing values with plausible estimates.

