#### 2.1.3. Eligibility Criteria

Inclusion criteria:Healthy neonates;Breech presentation;Sulcus angle ≥ 159° in ultrasound;

Exclusion criteria:Older than three months of age;Cerebral palsy;Developmental dysplasia of the hip: pathological alpha angle according to Graf classification (except type IIa) in ultrasound, or clinical criteria: positive Barlow’s or Ortolani’s test, hip clicks, tightness of adductors, asymmetry of the skin folds;Developmental alterations;Chromosomopathies;Other pathologies that could be adversely affected by the introduction of the Pavlik harness.

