#### 2.1.8. Outcomes

Outcomes measures will be collected two months after the first visit.

Primary outcome measures:The difference in the means of the sulcus angle between the two treatment arms at two months.

Treatment success is defined as a sulcus angle < 159° visualized by ultrasound. A sulcus angle ≥ 159° is the value set to diagnose TD in our study population, and values < 159° are considered non-dysplastic.

For newborns, radiographs and CT are not optimal imaging modalities. Besides X-ray radiation, the patellofemoral joint is not ossified, so it is not visible [36]. MRI is not an optimal screening tool because of the need for sedation, limited availability, and costs. Ultrasound allows for the visualization of cartilage and bone and is a faster, cheaper, and more available technique, so it could be used as a screening tool for detecting TD [37]. An ultrasound sulcus angle > 159° is considered dysplastic in newborns [28].

In our study, the ultrasound will be performed by a single observer in all cases to eliminate any possible inter-observer variability.

Secondary outcome measures:The difference in the means of the sulcus angle at baseline and after two months for each group;The difference will be measured by comparing the mean sulcus angle before and after the two-month treatment for the intervention group and the baseline and after two months for the control group.

The difference between the two treatment arms will be measured by comparing the proportion of patients in each treatment group with dysplastic (≥159°) and non-dysplastic (<159°) sulcus angles.

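### The primary between-arm test has no baseline covariate, and the Outcomes and Statistical Methods sections do not agree on whether it compares two-month angles or change from baseline

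*Protocol article*

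**What the plan says.** - **Primary outcome.** Protocol article, section 2.1.8, defines it as "The difference in the means of the sulcus angle between the two treatment arms at two months". This is a comparison of follow-up values.
- **Primary test.** Section 2.3.3 says the intervention arm's results "will be compared to the control group with the Student’s t-test for independent data". No covariate is attached to this test.
- **Endpoint wording.** The same section says the primary efficacy endpoint is "measured by analyzing the initial ultrasound sulcus angle data and those obtained after the treatment period".
- **Success rule.** It requires a statistical difference "in the knee SA between the treatment and control groups before and after treatment".
- **Baseline availability.** Section 2.1.3 lists "Sulcus angle ≥ 159° in ultrasound" as an entry criterion, so every randomised infant has a baseline value.
- **Other uses of baseline.** Section 2.3.3 plans paired t-tests within each arm, which do not compare the arms. It also plans one regression "while accounting for other factors that may affect the knee SA"; baseline angle is neither named there nor excluded.
- **Sizing.** Section 2.1.10 uses an unadjusted two-group formula (SD 5.78, difference 10°, 80% power, alpha 0.05) and arrives at six per group as a minimum.

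**The concern.** There are two linked problems.

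The first is scale. Section 2.1.8 points to two-month values. The two sentences in section 2.3.3 can be read as a t-test on two-month values, a t-test on change, or separate between-arm tests at both time points. The first two can give different p-values and intervals from the same data. The third would include a test at baseline, where randomisation already guarantees that any difference is due to chance. A reader cannot tell which result decides the trial.

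The second is efficiency. With about six infants per arm, the arms can differ noticeably at baseline by chance. An unadjusted comparison of two-month angles carries that difference forward in proportion to the slope of follow-up on baseline. No stated between-arm model uses the baseline to remove it, although the measurement is already in hand.

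**Working it through.** **Inputs.** SD 5.78°, difference 10°, alpha 0.05 and 6 per arm come from section 2.1.10. Two-sided testing is assumed, because it reproduces the plan's figure. The correlation ρ between baseline and two-month angle within the enrolled sample is not in the document, so a range is assumed.

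**Plan's own figure.** n = 2(1.96 + 0.842)² × 5.78² / 10² = 5.25 per group, rounded up to 6. This reproduces. The formula is a normal approximation. With the t distribution, the standard error at 6 per arm is 5.78 × √(2/6) = 3.34°, the noncentrality is 10/3.34 = 3.00, and the critical value on 10 df is 2.228. Power is 77.0%.

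**Three candidate analyses at 6 per arm.**
- t-test on two-month values: SD 5.78, 10 df, whatever ρ is.
- t-test on change: SD = 5.78 × √(2(1 − ρ)), 10 df, if both time points have the same SD.
- ANCOVA: residual SD = 5.78 × √(1 − ρ²), 9 df, with the standard error inflated by about √(1 + 1/8) for estimating the slope. At ρ = 0.5 the residual SD is 5.01, the standard error is 5.01 × 1.061 × √(2/6) = 3.07, the noncentrality is 3.26, the critical value is 2.262, and power is 83%.

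Power for a 10° effect (ANCOVA column by simulation):

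| ρ | Two-month t-test | Change t-test | ANCOVA |
|---|---|---|---|
| 0 | 77% | 48% | 72% |
| 0.3 | 77% | 63% | 76% |
| 0.5 | 77% | 77% | 83% |
| 0.7 | 77% | 94% | 94% |

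ANCOVA and the two-month t-test break even at ρ of about 0.35.

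**Chance imbalance.** If the baseline SD were also 5.78, the between-arm baseline difference would have a standard error of 3.34° and exceed 5° in about 13% of trials (5/3.34 = 1.50). With a slope of 0.5, a 5° imbalance moves the two-month difference by 2.5°, a quarter of the target effect.

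**Effect of the entry cut.** Suppose 5.78 is the SD before selection and the top 10% enter, the share that section 2.1.10 gives for a pathological angle among breech births. The baseline SD then falls to about 2.4° and the imbalance standard error to 2.4 × √(2/6) = 1.4°. Unselected correlations of 0.5, 0.6, 0.7 and 0.8 become about 0.23, 0.29, 0.37 and 0.48. With follow-up SD held at 5.78, ANCOVA power is about 74%, 75%, 78% and 82%, against 77% for the t-test. The change score also does better here than in the table: at ρ = 0.37 its SD is √(5.78² + 2.4² − 2 × 0.37 × 5.78 × 2.4) = √28.9 = 5.4.

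**The case against.** The t-test matches both the outcome definition and the sample-size formula. Under 1:1 randomisation it is unbiased and keeps its 5% error rate, because chance baseline variation is already in its standard error. A reader might infer that it confuses imbalance with effect and is therefore invalid. The document does not support that; only precision, and protection in an unluckily unbalanced trial, are at stake.

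A reader might also infer that the plan ignores the baseline altogether. That goes too far. The endpoint and success sentences in section 2.3.3 mention the initial angle, and a change-score test would use it. What stands is that no stated between-arm model says how it is used, and that those sentences do not fit section 2.1.8.

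A third tempting reading is that the regression on other factors must overfit 12 infants. The document does not say which variables enter. Section 2.3.1 lists variables to be recorded, not model terms, and arm plus baseline angle would leave 9 residual df. Naming the covariates of a non-primary model is also commonly left to a fuller document. No criticism of that regression is made here.

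The strongest objection is that the gain is uncertain. The correlation is unknown, the entry cut may lower it, and below about 0.35 ANCOVA loses a little power. This stands and limits the claim. Six per group is also a stated minimum; with more infants, the cost of one degree of freedom shrinks.

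**Conclusion.** The point holds as a recommended improvement and a needed clarification. It is not a claim of invalidity. The between-arm primary test is unadjusted although baseline is measured in everyone, and sections 2.1.8 and 2.3.3 leave the scale of that test open.

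The choice of scale alone can move power between 48% and 94% over ρ from 0 to 0.7, if the SDs at the two time points are equal. Against the two-month t-test's 77%, ANCOVA gains about 6 points at ρ = 0.5 and 17 at 0.7. It loses about 1 point at 0.3 and 5 at 0. These figures rest on SD 5.78, a 10° effect, 6 per arm, two-sided 0.05, and correlations that the document does not give. If the entry cut truncates baseline strongly, the expected result is close to break-even. The case for ANCOVA then rests mainly on fixing one scale and guarding against imbalance at small cost.

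**What to change.** In section 2.3.3, name one primary analysis: a linear model (ANCOVA) of the two-month sulcus angle on arm and baseline sulcus angle, reporting the adjusted between-arm difference with its 95% confidence interval. Reword the endpoint and success sentences there, and the outcome definition in section 2.1.8, so that all refer to the two-month angle compared between arms with adjustment for baseline. Keep the unadjusted t-test on two-month angles as supportive. Settle this before outcome data are examined by arm.

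The cost is a few sentences and one degree of freedom (10 to 9 at six per arm). The worst case is about 5 points of power (77% to 72%) if baseline and follow-up are nearly uncorrelated.

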#### 2.1.1. Trial Design

The study is designed as a prospective, randomized, controlled, triple-blinded, superiority clinical trial with two parallel groups and a primary endpoint of trochlear dysplasia screening and treatment over two months. Randomization will be performed as block randomization with a 1:1 allocation.

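### The rule for declaring the harness effective does not match the primary outcome: read literally it needs a baseline difference, and read charitably it leaves open whether the two-month angle or the change is tested

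*Protocol article*

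**What the plan says.** All references are to the protocol article.

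- **Section 2.1.8, Outcomes**, gives the primary outcome as "The difference in the means of the sulcus angle between the two treatment arms at two months". The abstract states the same objective. The before-to-after comparison, "The difference in the means of the sulcus angle at baseline and after two months for each group", is listed as secondary.
- **Section 2.3.3, Statistical Methods**, describes the primary efficacy endpoint as "measured by analyzing the initial ultrasound sulcus angle data and those obtained after the treatment period", which brings in the baseline scan. The test is a comparison of the intervention group "compared to the control group with the Student’s t-test for independent data". The next sentence gives the rule: the intervention is effective if it achieves "statistical differences (with a 95% confidence) in the knee SA between the treatment and control groups before and after treatment".
- **Section 2.1.1, Trial Design**, speaks of "a primary endpoint of trochlear dysplasia screening and treatment over two months", which names no variable and no contrast.
- **Section 2.1.10, Sample Size**, uses a single between-group difference in means of 10°, with σ = 5.78, 80% power and alpha 0.05. It gives n = 5.25, so a minimum of six per group.
- **Section 2.2.1, Allocation**, places randomisation after the baseline angle has been measured.

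**The concern.** The sentence that decides whether the harness worked should test the stated primary outcome, and here it does not. It adds a *before* condition that no other part of the article supports. If that condition is applied, an effective harness would almost always fail. If it is set aside as awkward wording, the reader must choose between a t-test on the two-month angle and a t-test on the change from baseline. In a trial whose stated minimum is 12 infants, those tests can easily give opposite answers. A choice left open until the data are seen also weakens control of the 5% error rate.

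**Working it through.** **Inputs from the article:** difference 10°; σ = 5.78; alpha 0.05; 80% power; six per group; 1:1 randomisation after the baseline scan.

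**Assumed, because the article does not give it:** the correlation r between baseline and two-month angle, taken over 0 to 0.9. Angles are taken as normal with SD 5.78 at both times.

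**1. The plan's own figure.** n = 2(1.96 + 0.8416)² × 5.78² / 10² = 2 × 7.849 × 33.41 / 100 = 5.24. This agrees with the stated 5.25 to rounding, and rounds up to six. It is reproduced only with a two-sided alpha and with 5.78 read as a standard deviation, although the text calls it a variance. The calculation covers one contrast, which fits the primary outcome in section 2.1.8.

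**2. The two-month comparison alone.** The noncentrality is 10 / (5.78 × √(2/6)) = 3.00 on 10 degrees of freedom, with critical value 2.228. Exact t-test power is 77%. The normal approximation gives 85%.

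**3. The literal rule (significant at baseline and at two months).** No true baseline difference exists after randomisation, so the baseline test is significant in about 5% of trials. The joint probability cannot exceed that at any effect or sample size. Over 200,000 simulated trials per scenario, with a true 10° effect and six per arm, the rule succeeds in about 3.8% of trials at r = 0, 3.6% at r = 0.5 and 3.0% at r = 0.9. With 20 per arm it is still about 5%.

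**4. The two charitable readings.** The SD of the change is 5.78 × √(2(1 − r)). At six per arm with a true 10° effect:

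| r (assumed) | SD of change | Power, change | Power, two-month angle | Tests disagree |
|---|---|---|---|---|
| 0 | 8.17 | 48% | 77% | 35% |
| 0.3 | 6.84 | 63% | 77% | 29% |
| 0.5 | 5.78 | 77% | 77% | 26% |
| 0.7 | 4.48 | 94% | 77% | 23% |
| 0.9 | 2.58 | about 100% | 77% | 23% |

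Even at r = 0.5, where the two powers are equal, the tests disagree on significance in about a quarter of trials.

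**5. Cost of choosing afterwards.** With no true effect, each test alone is significant in 5% of trials. At least one is significant in about 8.5% (r = 0) to 9.7% (r = 0.9).

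**The case against.** The strongest reply is that the primary endpoint can be identified. The abstract, section 2.1.8 and the sample-size contrast agree, and an independent-samples t-test fits them. The Trial Design phrase is loose wording and not a rival variable that anyone could analyse. The *before* in the rule is most naturally clumsy English for comparing the groups on their before-to-after results. Most of this stands. It does not settle the matter, because that natural reading points to the change, whereas section 2.1.8 points to the two-month value.

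A reader might infer three stronger points that the article does not support:

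- **That the trial will in practice succeed only 3–4% of the time.** Nothing else in the article asks for a baseline difference. The figure describes the sentence as written, not the trial's likely behaviour.
- **That a larger angle in the harness arm would count as effective.** The rule sentence names no direction, but the sentence before it does: "To determine if the Pavlik harness is more effective in reducing knee SA compared to no treatment". The trial is also described as a superiority design.
- **That this is the only success criterion.** Section 2.1.8 adds "Treatment success is defined as a sulcus angle < 159° visualized by ultrasound", and section 2.3.3 compares those proportions with Fisher's exact test. It also plans a within-group paired test.

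Two limits on the figures also stand. The correlations are assumed. Eligibility at 159° or more truncates the baseline angles, so a normal baseline with SD 5.78 is a simplification. A skewed (exponential) baseline gave a significant baseline difference in 4.1% of trials, so the ceiling near 5% is not an artefact of normality.

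**Conclusion.** The point holds as a mismatch between the success rule and endpoint sentence in section 2.3.3 and the primary outcome and sample size elsewhere in the article. The literal wording is unworkable. The practical problem is the unsettled choice between the two-month angle and the change: the power of the second relative to the first depends on an unknown correlation, the conclusions differ in roughly a quarter to a third of trials at the planned effect, and the error rate nearly doubles if the choice is made after seeing the data. These sizes assume six per arm (the stated minimum), equal normal SDs of 5.78 and correlations of 0 to 0.9. The mismatch itself needs no assumption. It should be corrected before any outcome data are examined.

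**What to change.** 1. In sections 2.1.1 and 2.3.3, state the primary endpoint as in section 2.1.8: the between-arm difference in mean sulcus angle at two months. Remove screening from the endpoint.
2. In section 2.3.3, delete *before and after treatment* and reword the rule: *The harness is declared effective if the two-sided 95% CI for the between-arm difference in mean sulcus angle at two months (harness minus control), from the independent-samples t-test, lies wholly below 0.* This also puts the direction of benefit into the rule.
3. Keep the before-to-after comparisons as secondary.

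This costs wording only. It keeps the planned t-test and matches the existing sample-size contrast.

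Optionally, the baseline-adjusted difference (ANCOVA) could become the primary analysis. That is a change of analysis, not of wording: the Student's t-test sentence must then be changed as well, and one degree of freedom is spent (10 to 9 with six per arm).

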#### 2.1.9. Participant Timeline

During the first four to six weeks of life, a bilateral knee ultrasound will be performed on neonates with a breech presentation to determine the sulcus angle. Then, they will be derived into the Pediatric Orthopedics and Traumatology Department, as stated in Figure 2.

Intervention group: The estimated duration of the Pavlik harness procedure is two months, with four-week revisions by a pediatric orthopedic surgeon. After two months, a pediatric radiologist will perform a second ultrasound to evaluate the sulcus angle, and the Pavlik harness will be removed. In both groups, a face-to-face consultation in pediatric orthopedic surgery will be performed at 6–9 months to assess the clinical progression, as shown in Figure 3.

Control group: the control group will be evaluated two months after the baseline ultrasound, with a second one performed by a pediatric radiologist, as shown in Figure 4.

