#### 2.1.10. Sample Size

The study population are the newborns at TD of Virgen de la Arrixaca University Hospital. The total number of births in this institution in 2016 was 14,167. However, the frequency of TD in newborns is unknown.

Breech presentation is a risk factor for TD, and the frequency of breech presentation is between 3–5% [38]. We consider 5% to be the estimated frequency of this presentation at birth, which implies that approximately 708 newborns each year have a breech presentation in our population. TD (a pathologic sulcus angle) is identified in 10% of the breech presentation population [28]. Accordingly, we consider the number of newborns in our population with TD to be 71 per year.

For the ultrasound screening test, we need 116 ultrasounds to have a 95% confidence that the real value is within ±5% of the measured one. This estimation was calculated according to the following formula:$$n=\frac{\;\frac{Z_{\alpha }^{2}\cdot p\cdot \left(1-p\right)}{e^{2}}}{1+\left(\frac{Z_{\alpha }^{2}\cdot p\cdot \left(1-p\right)}{e^{2}\cdot N}\right)}$$
where *Z_α_* is the critical value of the normal distribution (for a confidence level of 95%, *α* is 0.05, and the critical value is 1.96), *e* is the margin of error (*e* = 5%), *p* is the sample proportion (*p* = 10%), and *N* is the population size (*N* = 708). Note that a finite population correction has been applied to the sample size formula.

For the estimation of the treatment groups sample size, the following formula is applied: $$n=\frac{2{\left(a+b\right)}^{2}\;\sigma^{2}}{{\left(\mu_{1}-\mu_{2}\right)}^{2}}$$
where *n* is the sample size in each group, a is the conventional multiplier for alpha, b is the conventional multiplier for power, σ is the sample variance, and *μ*_1_ − *μ*_2_ is the difference we aim to detect. The sample variance was calculated from a pilot study, from which we obtained a value of *σ* = 5.78.

To consider a difference of 10° in sulcus angles between the treatment and the control group as clinically significant (*μ*_1_ − *μ*_2_) and be detected with 80% power and a significance level alpha of 0.05, *n* = 5.25. That means six subjects per group is the minimum sample size.

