## Figures and Tables

**Figure 1 jpm-13-00796-f001:**
[figure not shown]
Study design. The newborns in the breech position will be screened with an ultrasound test for dysplastic sulcus angles (≥159°). Then, they will be divided into a 1:1 randomization, either into the intervention group or the control group. A blinded observer will perform a second ultrasound, from which the data for the outcomes will be collected.

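### A within-arm paired t-test is used to judge whether the harness works, although infants are selected on a high reading of the same angle, so regression to the mean favours a fall even with no effect.

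*Protocol article*

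**What the plan says.** All references are to the protocol article.

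- **Section 2.3.3 (Statistical Methods)** gives the paired analysis an efficacy purpose: "To assess if the Pavlik harness is effective in reducing the knee SA within the treatment group, the Student’s t-test for dependent data" compares baseline with two months, and is run in each group.
- **Section 2.1.8 (Outcomes)** lists the same contrast as a secondary outcome: "The difference in the means of the sulcus angle at baseline and after two months for each group".
- **Section 2.1.3 (Eligibility Criteria)** sets the entry condition on that same variable: "Sulcus angle ≥ 159° in ultrasound".
- **Figure 1 legend** describes the qualifying scan: "The newborns in the breech position will be screened with an ultrasound test for dysplastic sulcus angles (≥159"°).
- **Section 2.1.9 (Participant Timeline)** times follow-up from baseline: "the control group will be evaluated two months after the baseline ultrasound". No baseline scan separate from the screening scan is described.

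The primary outcome in section 2.1.8 is the between-arm difference in mean angle at two months. Section 2.3.3 tests it with the independent-samples t-test.

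**The concern.** A paired t-test asks whether the mean change is zero. That is the right null hypothesis for a harness with no effect only if untreated infants would show no change on average. Here they would be expected to show a fall. Infants enter because one reading of the outcome variable was high, and some of those readings are high partly through scan-to-scan variation. When the scan is repeated, that part does not carry over, so the average drops whenever the test-retest correlation is below 1.

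The drop is expected equally in both arms. A comparison between arms cancels it. A before-after test within the harness arm counts it as benefit. If the plan is followed as written, a significant paired test in the harness arm could be reported as evidence that the harness works when the fall comes from selection alone.

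**Working it through.** **Inputs from the document**
- SD 5.78°, from section 2.1.10: "The sample variance was calculated from a pilot study, from which we obtained a value of" 5.78. The pilot population is not described.
- Fraction above the cut, from section 2.1.10: "TD (a pathologic sulcus angle) is identified in 10% of the breech presentation population".
- Entry cut 159° (section 2.1.3).
- Difference to detect 10°, alpha 0.05, power 80%, minimum six per group (section 2.1.10).

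**Assumptions not in the document**
- Angles are normally distributed across breech infants, and 5.78° is the SD in that whole population.
- The test-retest correlation r is 0.9, 0.8 or 0.7, with 0.95 and 0.5 as outer values.
- There is no treatment effect and no growth effect.

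**Step 1: the plan's own figure.** n = 2 × (1.960 + 0.842)² × 5.78² / 10² = 5.24. The article gives 5.25. Both round up to six per group, so the figure reproduces.

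**Step 2: how extreme the selected infants are.** The upper 10% of a normal distribution starts at z = 1.2816.
- Population mean: 159 − 1.2816 × 5.78 = 151.6°.
- Normal density at that z divided by 0.10: 1.755.
- Mean of eligible infants: 151.6 + 1.755 × 5.78 = 161.7°.
- Excess over the population mean: 1.755 × 5.78 = 10.14°.

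**Step 3: expected fall with no treatment effect.** Fall = (1 − r) × 10.14°.

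**Step 4: how often each test is significant with no effect.** These rates come from simulation, with 20,000 to 40,000 trials per setting. Infants are drawn from the upper 10%, and the second reading is generated with correlation r. The paired test is counted when it shows a significant fall at two-sided 5%, which is nominally 2.5% in that direction.

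| r | Expected fall in each arm | Paired test, n = 6 | Paired test, n = 20 |
|---|---|---|---|
| 0.95 | 0.5° | 8% | 22% |
| 0.9 | 1.0° | 12% | 40% |
| 0.8 | 2.0° | 21% | 69% |
| 0.7 | 3.0° | 30% | 87% |
| 0.5 | 5.1° | 50% | 99% |

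The independent t-test between arms at six per group stays at about 5% for every r in the table.

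**Step 5: sensitivity.** With SD 4° or 8° in place of 5.78°, the false-positive rates agree within simulation error, while the fall in degrees scales with the SD. The n = 20 column matters because six is stated as a minimum: more infants make the paired test's error worse.

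**The case against.** The strongest reply is that section 2.3.3 already has a between-arm rule for effectiveness, placed just before the paired test, and that the paired test serves only a secondary outcome. This stands and limits the point to that secondary analysis. It does not remove it, because the next paragraph gives the paired test its own effectiveness purpose.

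A second reply is that a single observer performs every scan and that the Introduction describes the cartilaginous angle as nearly constant from birth to adolescence. A single observer removes differences between observers but not variation between repeat scans by the same person. A stable true angle does not help either, since selection also acts on measurement error. The reply does hold on size: r is unknown, and at r = 0.9 the expected fall is 1.0° against the 10° difference the trial aims to detect.

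A reader might infer four stronger things that the document does not support:

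- **That the success endpoint is biased because entry and success share the 159° cut.** Section 2.1.8 says "Treatment success is defined as a sulcus angle < 159° visualized by ultrasound", and some untreated infants will cross that line. But the planned Fisher test compares success between randomised arms, and under no effect the crossing is expected equally in both.
- **That the plan would read significance in the harness arm without significance in control as efficacy.** No section sets that rule. The plan only runs the paired test in each group.
- **That the primary test is weak, making the paired test a likely fallback.** A t-based calculation gives 77% power at six per group if 5.78° is the SD among randomised infants. The degree figures above instead take 5.78° as the SD among all breech infants. Under that model the between-arm power for 10° is about 94% to over 99% for r from 0.7 to 0.9. The two arguments cannot be combined.
- **That maturation adds to the fall.** The Introduction's statement on the cartilaginous angle gives no support for this.

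**Conclusion.** The concern holds for the within-arm paired test as a test of effectiveness, and for nothing beyond it. For r between 0.9 and 0.7, selection alone gives an expected fall of 1.0° to 3.0° in each arm. It also raises the chance of a false significant reduction at six infants from 2.5% to about 12% to 30%. These figures rest on normality, on 10% of breech infants lying at or above 159°, on the screening scan serving as the baseline, and on an assumed r. The degrees also depend on SD 5.78° applying to all breech infants; the error rates hardly depend on it. The direction of the bias needs only r below 1. A significant fall is more likely than it should be, but not certain. The primary between-arm test and the Fisher comparison of success are unaffected.

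**What to change.** 1. In section 2.3.3, remove the statement that the within-arm paired test assesses whether the harness is effective.
2. Keep the within-arm change in section 2.1.8 as a secondary outcome, but report it descriptively for each arm as a mean with 95% CI, without a test.
3. State in section 2.3.3 that effectiveness is judged only from the between-arm comparison.

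This is a change of wording only. It needs no extra infants, scans or data, and gives up one p-value per arm.
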